### Ethical considerations

There are a number of ethical considerations that have been taken into account in the preparation of this protocol. These are as follows:

#### Recruiting adults only

Remploy only work with people who are older than 16 and in the work market.

#### Consent

After expressing an interest in the study, potential participants will be asked to complete an eligibility pack, which will include a participant information sheet along with a consent form. Participants will have the opportunity to ask questions about the study by phone, email or post before being asked to complete the consent form. Until eligibility has been assessed and informed consent has been given, individuals will not be able to begin participation in the study.

#### Confidentiality

Data collected by Remploy will be kept and stored in accordance with their usual internal procedures. Data collected by the research team will be kept either on fingerprint or password-locked memory sticks, on fingerprint identification laptops, stored in a locked filing cabinet in the researcher’s office on the site of Gartnavel Royal Hospital, or will be saved on a secure network space that only the researchers have access to. Personally identifying information will be removed from the main electronic data files for analysis by the researchers at the Robertson Centre for Biostatistics, University of Glasgow. A coded file with sensitive data will be stored separately.

### Baseline data collection

The standard information routinely gathered by Remploy will be used as baseline data. This will include demographic and employment information. In addition, mood and social functioning will be assessed via the Patient Health Questionnaire (PHQ-9—depression) [13], Generalised Anxiety Disorder Scale (GAD-7—anxiety) [14] and the Work and Social Adjustment Scale (WSAS—five-item social functioning scale) [15]. Current and recent medical treatment including medication will also be recorded.

### Follow-up data collection

The main follow-up point will be at 3 months with an additional follow-up assessment at 6 months. The data will be used to:Determine the proportion of people taking up the LL intervention, adherence to the intervention and follow-up rates.Describe the difference in proportion of people in work at 12 weeks between the LL group and the TAU control group or if not in work the number of interviews attended and job submissions made (measuring motivation).Describe the subsequent number (frequency) and total (days) off work over 3 months and 6 months in both arms comparing within group comparisons from baseline, and between-groups at 3 and 6 months.Describe and compare impact on mood, social function and satisfaction at 3 months and 6 months in both arms comparing within group comparisons from baseline, and between-groups at 3 and 6 months. This data will be used for the future sample size calculation.

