## Methods/design

### Overview

This is a feasibility study to test the possibility of delivering the Living Life (LL) online life skills resource in Remploy. In this RCT, 50% of participants will be randomly allocated to the immediate group (IA) and will receive LL immediately. The remaining 50% of participants will be allocated to the delayed access control (DAC) group. Both arms receive treatment as usual. The primary end point is 3 months at which point the control arm will be provided with access to LL if they wish. Monitoring will continue up to a 6-month final exit point.

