### Participants

The aim is to recruit 100 participants in total for this feasibility study, 50 intervention participants and 50 control participants to allow for comparison at the 3-month follow-up point and 6-month exit point. We will recruit males and females aged 16 +.

*Inclusion criteria:* Participants will be willing to take up the offer of LL and appropriate for usual Remploy support—and with no active risk to self at initial Remploy assessment (this is not routinely investigated, but if suicidality is disclosed at the initial assessment, the individual will not enter the study). Individuals must be able to register on the website, read and understand the LL resources via the internet or DVD; at home or in the Remploy office.

*Exclusion criteria:* Individuals will be excluded if they are unwilling or unable to use the LL approach and/or if they are at active risk of suicide, identified in which case usual care (referral to GP) will occur as is normal Remploy practice.

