### Statistical analyses

Baseline characteristics will be summarised for all participants as well as for the IA and DAC groups separately. Participant uptake and adherence to the online intervention, defined as the number of online sessions completed and the number of support sessions participants took part in, as well as data follow-up rates, will be summarised and presented as percentages.

To assess efficacy, repeated measures analysis will be carried out using an intention to treat approach by means of a linear mixed effects model with the time (baseline, 3 months, 6 months) and group (control, intervention) main effects and their interaction as fixed effects, and participant as a random effect. Models will be adjusted for age, gender and antidepressant use at baseline. Tukey post-hoc comparisons will be carried out with a familywise error rate of 5%. These models will be used to estimate and test the statistical significance of the within-group differences between time points and the between-group differences at each time point. Finally, a power calculation will be carried out to determine the required sample size for a future RCT.

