### Determining the feasibility of the study design

As outlined in the aims sections, the feasibility of the trial design will be determined by considering four main factors: recruitment, adherence, acceptability and follow-up rates. In the future RCT, the recruitment period is estimated to be 6 months, with the aim of recruiting approximately 100 people in total. Therefore, an acceptable recruitment rate in the current feasibility study is 3–4 participants per week for 6 months.

The adherence rate is defined as the number of online modules completed. We have examined completion rates of equivalent modules delivered in face to face classes. In our pilot study 65% of people attended half of face to face sessions [7]. We judge an acceptable completion rate as 55% of people completing four or more of the eight course modules. The number of support sessions participants take part in will also be used as an indicator of engagement and will provide information regarding the feasibility of the caseloaders taking on this role.

As discussed in the “Methods/design” section, we will be using the Client Satisfaction Questionnaire to assess acceptability of the intervention. Scores on this measure range from 8–32 with a median of 20. For this study scores ≥20 will be considered as acceptable.

Finally, in relation to the feasibility of collecting data, the main outcomes relating to employment are collected by Remploy as part of their standard procedures, so we expect to have approximately 100% follow-up rate for these variables (number of applications, employment status etc.) The remaining data concerning mood will be collected by the researcher. From our knowledge and experience of online trials, we believe a follow-up rate of ≥70% is acceptable for secondary outcomes; therefore, this follow-up rate would indicate feasibility of data collection.

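### Interview and job-submission counts are compared only among people not in work at 12 weeks; the arm with more people in work can then look less motivated, if the package raises the success of each submission

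*Protocol article*

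**What the plan says.** The employment item under Follow-up data collection has two parts. The first is "Describe the difference in proportion of people in work at 12 weeks between the LL group and the TAU control group". The second continues the same sentence: "or if not in work the number of interviews attended and job submissions made (measuring motivation"). The conditional clause sets the population for the counts, and the bracket sets their interpretation. No other section plans these counts in everyone randomised.

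Three other places bear on the point:
- Participants gives the planned size: "The aim is to recruit 100 participants in total for this feasibility study, 50 intervention participants and 50 control participants".
- Determining the feasibility of the study design says that "the main outcomes relating to employment are collected by Remploy as part of their standard procedures". It anticipates almost complete data on them, about 100%, and gives applications and employment status as examples.
- Statistical analyses states intention to treat for the efficacy analysis, which is a linear mixed model over baseline, 3 and 6 months. It does not mention interviews or submissions.

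**The concern.** Applying and being interviewed is how people get jobs. The more active job-seekers are therefore the likelier to be in work at 12 weeks, and so to drop out of the group in which activity is counted. If one arm has more success per submission, it loses more of its active people. Randomisation no longer protects the comparison of those who remain.

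The Discussion expects that the package might help both job-seeking and employment, so the distortion could arise just when the package does what is hoped. The stake is interpretive. A figure labelled as motivation could point against the arm that got more people into work, and that outcome definition could be carried into the later full trial, which is meant to study employment status as well as mood.

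**Working it through.** The article gives no employment rate, no submission counts and no calculation for this outcome, so there is no figure of the plan to reproduce. Everything below except the 50 per arm is an assumption, used to show direction and plausible size.

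**Hand arithmetic, 50 per arm.** In each arm 25 people make 10 submissions and 25 make 2, so the mean is 6.0 in both.
- Control: 12 find work (10 high, 2 low). Left: 15 high, 23 low. Mean (150 + 46)/38 = 5.16.
- Living Life: 20 find work (18 high, 2 low). Left: 7 high, 23 low. Mean (70 + 46)/30 = 3.87.

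Activity is identical, yet the arm with more people in work shows the lower mean.

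**Model.** Weekly submission rates vary between people as a gamma distribution with mean μ and coefficient of variation (CV) 0.8, so k = 1/0.8² = 1.5625. Each submission leads to a job with probability p. Over 12 weeks, with q = k/(k + 12μp):
- share in work = 1 − q^k
- mean 12-week submission rate among those not in work = 12μq

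| Scenario | μ | p | In work | Mean, not in work | Ratio to control | True ratio |
|---|---|---|---|---|---|---|
| Control | 1.0 | 0.02 | 20.0% | 10.40 | – | – |
| Living Life: success up, activity equal | 1.0 | 0.035 | 31.1% | 9.46 | 0.909 | 1.00 |
| Living Life: success up, activity +10% | 1.1 | 0.035 | 33.3% | 10.19 | 0.979 | 1.10 |
| Living Life: success unchanged, activity +10% | 1.1 | 0.02 | 21.6% | 11.29 | 1.086 | 1.10 |
| Living Life: success unchanged, activity +20% | 1.2 | 0.02 | 23.2% | 12.16 | 1.169 | 1.20 |

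For equal activity, the spurious deficit runs from 4% (CV 0.6, Living Life p = 0.03) to 13% (CV 1.0, p = 0.035). The observed count in people with no success is (1 − p) times the tabulated mean: 10.19 v 9.13 in the equal-activity case, much the same picture.

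**Size against noise.** Simulating 20,000 trials of 50 per arm on this model, Living Life has the lower not-in-work count in 71% of trials when activity is equal, where an undistorted comparison would give about 50%. With activity +10% and higher success it is 57%; with activity +10% and unchanged success it is 33%. The difference between arms has a between-trial standard deviation of about 1.9 in the equal-activity case, larger than the shift of about 1 submission.

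**A second model** (control 11% to 35% in work, success per submission multiplied by 1, 1.5 or 2) agrees. Equal activity with higher success gives −0.4 to −2.2 submissions among those not in work. No effect on either gives no difference. With 20% more submissions (true difference +2.4) and unchanged success, the difference stays positive, at +1.0 to +2.1.

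**Would a raw 12-week count in everyone solve it?** Not if people stop applying once hired. The mean count up to hire is then (share in work)/p:
- control: 0.2001/0.02 = 10.0
- Living Life, equal activity: 0.3106/0.035 = 8.9, an 11% spurious deficit
- Living Life, activity +10%: 0.3329/0.035 = 9.5, still 5% below control

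Dividing by time spent searching helps. Mean search time is k/((k − 1)μp) × (1 − q^(k−1)), that is 10.73 weeks in control and 9.95 in the equal-activity Living Life arm. The pooled rates are 10.00/10.73 = 0.93 and 8.88/9.95 = 0.89 per week. The spurious deficit falls from 11% to 4%, but does not vanish.

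**The case against.** The strongest case against is about weight. The item only describes; no test or decision rule attaches to interviews or submissions. Feasibility is judged on recruitment, adherence, acceptability and follow-up, and employment data enter there only through their completeness. The sentence on the future sample size most naturally belongs to the mood, function and satisfaction item. All of this stands and limits the severity.

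It can also be said that the sentence is a two-level description: who has a job and, for the rest, how close they are. A reader who sees the employment proportions alongside would hardly conclude that the better arm did worse. That is a fair reading of the layout, but it does not cover the label. The text offers the counts as a measure of motivation, and in this subgroup they cannot carry that meaning between arms.

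Two stronger readings are tempting and are not supported:
- A reader might infer that the restriction always biases against Living Life. It does not. With no effect on success or activity there is no bias, and with more submissions at unchanged success the gain is only attenuated. In the table, the deficit needs success per submission to rise by 75% (0.02 to 0.035).
- A reader might infer that the plan breaks its own intention-to-treat commitment. The statement "To assess efficacy, repeated measures analysis will be carried out using an intention to treat approach" introduces the mixed model and says nothing of these counts, so there is no contradiction.

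**Conclusion.** The point holds in conditional form. The counts are confined to a subgroup defined by a post-randomisation outcome, so a between-arm difference in them cannot be read as an effect on motivation. If the package raises success per submission, the arm with more people in work can look less active: about 9.5 v 10.4 submissions with identical activity, a deficit of 9% (4% to 13% over the assumptions tried). If it raises only submissions, the gain shrinks slightly and keeps its sign. The sizes rest wholly on assumed employment shares, submission rates and spread; the direction rests on active seekers being likelier to find work and on success per submission differing between arms. The feasibility conclusions are not affected. It is worth correcting because the article calls the employment data main outcomes and the label could pass into the full trial.

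**What to change.** In the employment item under Follow-up data collection:

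1. Compare all randomised participants on one ordered outcome: in work at 12 weeks as the best category, then number of interviews, then number of submissions. Use a rank or proportional-odds method with a confidence interval. Read the result as progress towards work, not as motivation alone, since an employment difference will dominate it.
2. If job-search activity is also described for everyone, give it as a rate per week of job search until starting work, not as a raw 12-week count. The rate reduces the distortion without removing it, so it too is descriptive.
3. Keep the not-in-work counts as description and drop their reading as an effect on motivation.

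The cost is mainly wording. The ordered outcome is less direct to read than a mean count. The article names only applications and employment status among the variables Remploy records, so the availability of interview counts and job start dates for everyone is an inference to confirm with Remploy.

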### Measures

The following measures will be used in the study.

### Patient Health Questionnaire-9

PHQ-9 [13] is a freely available mood rating questionnaire consisting of nine questions mirroring DSM-IV depression diagnostic criteria and each rated 0–3 giving a maximum score of 27. Cut-off scores are used to label depression severity as:0–4, minimal depression;5–9, mild depression;10–14, moderate depression;15–19, moderately severe depression;20–27, severe depression.

### Generalised Anxiety Disorder-7

The GAD-7 [14] is a seven-item questionnaire focusing on symptoms of anxiety experienced in the past 2 weeks. Each item is rated according to the frequency of the described problem. The responses are scored as follows: 0 = “not at all”, 1 = “several days”, 2 = “more than half the days”, 3 = “nearly every day”. Therefore, the maximum score is 21. Scores of 0–5 indicate mild anxiety, 6–10 = moderate anxiety, 11–15 moderately severe anxiety and 15–21 severe anxiety.

### Work and Social Adjustment Scale

The WSAS [15] will be used to assess levels of social functioning. The WSAS is a five-point questionnaire addressing life activities. The questionnaire probes issues relating to the impact the disorder in question is having on the individual’s everyday life and functioning. Responses are given on a scale of 0–8, with higher scores indicating higher level of impairment or disruption to social functioning. Therefore, the maximum score on this questionnaire is 40. Mundt, Marks, Shear and Greist [15] state that, in light of studies that included two clinical groups: in those with depression and those with OCD, a score below 10 on the WSAS does not indicate clinically significant problems and between 10 and 20 indicates significant impairment. Those scoring over 20 are likely to have significant problems in their social functioning [15].

### The Client Satisfaction Questionnaire

The Client Satisfaction Questionnaire (CSQ-8) will be administered post intervention as a measure of satisfaction [16]. The CSQ-8 is an eight-item questionnaire rated using a four-point Likert scale. Scores range from 8–32 with higher scores indicating greater satisfaction with the intervention in question.

### Statistical analyses

Baseline characteristics will be summarised for all participants as well as for the IA and DAC groups separately. Participant uptake and adherence to the online intervention, defined as the number of online sessions completed and the number of support sessions participants took part in, as well as data follow-up rates, will be summarised and presented as percentages.

To assess efficacy, repeated measures analysis will be carried out using an intention to treat approach by means of a linear mixed effects model with the time (baseline, 3 months, 6 months) and group (control, intervention) main effects and their interaction as fixed effects, and participant as a random effect. Models will be adjusted for age, gender and antidepressant use at baseline. Tukey post-hoc comparisons will be carried out with a familywise error rate of 5%. These models will be used to estimate and test the statistical significance of the within-group differences between time points and the between-group differences at each time point. Finally, a power calculation will be carried out to determine the required sample size for a future RCT.

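### The planned mixed model makes no use of the baseline score in the 3-month between-group difference, and it places that contrast in a Tukey family that is not defined

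*Protocol article*

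**What the plan says.** The Statistical analyses section specifies a "linear mixed effects model with the time (baseline, 3 months, 6 months) and group (control, intervention) main effects and their interaction as fixed effects", with "participant as a random effect". On covariates it says: "Models will be adjusted for age, gender and antidepressant use at baseline". The baseline value of the outcome scale is not among them, although Baseline data collection has PHQ-9, GAD-7 and WSAS all measured at entry.

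On multiplicity it says: "Tukey post-hoc comparisons will be carried out with a familywise error rate of 5" (per cent). The set of means or contrasts that form the family is not given. The models are to estimate and test "the within-group differences between time points and the between-group differences at each time point".

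The Overview fixes the main time point: "The primary end point is 3 months at which point the control arm will be provided with access to LL if they wish". The size is set under Participants: "The aim is to recruit 100 participants in total for this feasibility study, 50 intervention participants and 50 control participants". Determining the feasibility of the study design accepts 70% or more follow-up for the mood data. Research questions and Follow-up data collection say that the efficacy data will feed the sample size of a later trial.

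**The concern.** Two features of the analysis weaken the contrast that matters most for efficacy, which is the randomised comparison at 3 months, before the control arm is offered the package.

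First, when baseline is a response with a free group effect, the group difference at 3 months has its own unconstrained parameter. Randomisation tells us that the two baseline means are equal in expectation, and the model does not use that fact. A chance baseline difference then passes into the 3-month estimate, and the precision that the baseline score could give is lost.

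Second, the 3-month contrast is not set apart. It is listed with a baseline comparison of randomised groups, which tests nothing of interest, and with before–after tests inside each arm. In people recruited for low mood, those before–after changes mix any treatment effect with regression to the mean and natural recovery. One familywise procedure over such a list widens the interval for the useful contrast to pay for the others.

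At stake is the quality of the efficacy estimate and interval passed on to the planning of the later trial.

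**Working it through.** The article states no power, SD, effect size or interval width for this analysis, so there is no figure of its own to reproduce.

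**Inputs.** 50 per arm (Participants); 70% followed, so 0.70 × 50 = 35 per arm (Determining the feasibility of the study design); three visits, two groups, a random participant intercept and a 5% familywise rate (Statistical analyses). Assumptions: equal correlation ρ between visits, as a random intercept implies, read as the correlation left after the three covariates; ρ = 0.5–0.6 as the main range and 0.3 as a low value; outcome SD = 1; two-sided intervals.

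**1. Complete data.** Planned model: Var = 2/n, whatever ρ is. Common baseline mean, or baseline as covariate: Var = 2(1 − ρ²)/n. The reduction is ρ².

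| ρ | planned, n = 50 | baseline used | reduction |
|---|---|---|---|
| 0.3 | 0.0400 | 0.0364 | 9% |
| 0.5 | 0.0400 | 0.0300 | 25% |
| 0.6 | 0.0400 | 0.0256 | 36% |

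Fitting both models to 40 simulated complete trials (50 per arm, ρ = 0.6, no covariates) agreed. The planned model's 3-month estimate equalled the raw mean difference to rounding error (largest gap 1.6 × 10⁻¹⁵). Its standard error was 1.24 times that of the common-baseline model, against 1/√(1 − 0.36) = 1.25 in theory.

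The standard error of the chance baseline difference is √(2/50) = 0.20 SD. At ρ = 0.6, an imbalance of that size moves the unadjusted 3-month estimate by 0.6 × 0.20 = 0.12 SD.

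**2. 50 baselines and 35 followed per arm.** The random intercept now borrows from the baselines of those lost. Planned model: Var = 2[(1 − ρ²)/35 + ρ²/50]. Common baseline mean: Var = 2(1 − ρ²)/35.

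| ρ | planned | baseline used | reduction |
|---|---|---|---|
| 0.3 | 2(0.91/35 + 0.09/50) = 0.0556 | 0.0520 | 6.5% |
| 0.5 | 2(0.75/35 + 0.25/50) = 0.0529 | 0.0429 | 19% |
| 0.6 | 2(0.64/35 + 0.36/50) = 0.0510 | 0.0366 | 28% |

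The planned model therefore recovers part of the baseline information when follow-up is incomplete, but not all of it.

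**3. Tukey multiplier.** The width ratio is the familywise critical value divided by the ordinary t value. The t value is 1.972 at 196 degrees of freedom.

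| reading of the family | critical value | ratio |
|---|---|---|
| two groups, separately at each visit | 1.972 | 1.00 |
| three means | 2.362 | about 1.20 |
| the nine named contrasts | joint (simulated, against 1.96) or Bonferroni (2.804) | about 1.39 to 1.42 |
| all six group-by-time means (15 pairs) | 2.878 | 1.46 |

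The nine named contrasts are 2 arms × 3 pairs of visits = 6 within arms, plus 3 between arms. For the six-mean reading the ratio runs from 1.465 at 98 degrees of freedom to 1.454 in the limit.

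**4. Half-width of the 3-month interval, complete data, 50 per arm, SD units.** 0.576 with six-mean Tukey; 0.394 as a single unadjusted contrast; 0.344 (ρ = 0.5) or 0.318 (ρ = 0.6) as a single baseline-adjusted contrast.

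**The case against.** The strongest reply is that this is a feasibility study. The primary question is whether people can be recruited, randomised and followed; the success criteria are recruitment, adherence, acceptability and follow-up; no efficacy test decides anything. The planned estimate is also unbiased under randomisation, and its standard error already allows for chance imbalance. All of this stands. It makes the point an improvement in efficiency and not the correction of a wrong result.

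The same model could give a difference in change through the interaction. That is true, but the section names the difference at each time point. Change scores also help less: with complete data the variance is 4(1 − ρ)/n, which at n = 50 is 0.0400 for ρ = 0.5 and 0.0320 for ρ = 0.6, against 0.0300 and 0.0256 with baseline used.

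Several stronger readings are tempting and are not supported:

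- A reader might infer that the 3-month interval will be 46% too wide. The article does not say that Tukey covers all six means, and the contrasts it names number nine, not fifteen. The 46% comes from the multiplier alone and not from the missing baseline adjustment. A simultaneous interval is also wide by design, so the excess exists only relative to a single interval.
- A reader might take the 3-month mood contrast as the trial's primary outcome. The Overview names a time point only, and the feasibility section treats the mood data as secondary.
- A reader might infer a definite loss of power, or that an inflated SD will go into the future sample size. The article states no power and does not say which SD will be used. The random-intercept model yields the variance components from which an adjusted SD can be derived, and Tukey changes neither the point estimate nor the SD.

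The exact family may be left to an analysis plan that is not shown. What is open to comment is that the article commits the tests it names, the 3-month contrast among them, to a familywise rate without setting that contrast apart.

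**Conclusion.** The point holds as a free improvement. As written, the model leaves baseline unconstrained and does not adjust for it, so the 3-month difference makes no use of the baseline score when data are complete and only partial use when follow-up is missing. Using it would cut the variance by 25–36% (complete data) or 19–28% (50 baselines, 35 followed per arm) at ρ of 0.5–0.6, and by about 6–9% at ρ of 0.3. The size rests on an assumed correlation and on the compound symmetry of the planned model.

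On multiplicity, the main randomised contrast is grouped with comparisons that answer other questions. The cost in interval width lies between nothing and about 46%, depending on a family that the article does not state.

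**What to change.** In the Statistical analyses section:

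1. Constrain the two arms to a common baseline mean, with group-by-time terms only after baseline, or add the baseline value of each scale as a covariate in a model for the 3- and 6-month scores.
2. Name the 3-month between-group difference as the single main efficacy contrast for each scale, and report it with an ordinary 95% confidence interval outside the Tukey family.
3. Drop the baseline between-group test, and show within-arm changes as descriptive summaries without significance tests.
4. If Tukey is kept for any remaining comparisons, state which means or contrasts form the family.

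This changes wording only. No data, visits or participants are added. The only loss is the p-values for before–after changes.

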### Aims

This project aims to determine the feasibility of a randomised controlled trial (RCT) investigating an online CBT-based life skills resource for people who are seeking work and attending Remploy. It is an unfunded study to establish viability of applying for a substantive later funded RCT.

The aim of this study is to recruit people experiencing symptoms of depression. We will include both those with clinically diagnosed major depression as well as those with raised mood scores. We will describe the population in detail in terms of mood severity and clinical diagnosis (if known). The research questions of the study are outlined below.

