### Research questions

Primary question:Is the study design feasible—is it possible to recruit from Remploy, randomise participants and collect data at baseline, 3 months and 6 months?

Secondary questionsb.To what extent will participants adhere to the intervention?b.Is the Living Life package satisfactory/acceptable to participants?c.How many participants will be needed for a sufficiently powered future RCT? (Efficacy data at 3 and 6 months will be used for the future sample size estimation).

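### With participant as the only random effect, the efficacy model assumes one variance and one correlation across all three visits, so its standard errors can be wrong in either direction (minor)

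*Protocol article*

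**What the plan says.** The Statistical analyses section describes a "linear mixed effects model with the time (baseline, 3 months, 6 months) and group (control, intervention") and enters these "main effects and their interaction as fixed effects, and participant as a random effect". Baseline is therefore one of the modelled outcomes. No other random term, residual covariance structure or visit-specific variance is given. "Models will be adjusted for age, gender and antidepressant use at baseline".

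The models are to estimate and test the "within-group differences between time points and the between-group differences at each time point". On multiplicity: "Tukey post-hoc comparisons will be carried out with a familywise error rate of 5"%.

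The Overview makes 3 months the primary end point and lets the control arm have Living Life from then on. Under Research questions, the primary question is feasibility; the future sample size is a secondary question, for which "Efficacy data at 3 and 6 months will be used for the future sample size estimation". The planned size is 50 per arm (Participants section).

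**The concern.** A lone participant intercept with independent, equal-variance residuals fixes the within-participant covariance at two parameters. The standard error of a between-group difference at 3 months is then built from a variance averaged over visits, not from the 3-month variance. The standard error of any within-group change is built from one averaged correlation, whichever two visits are compared.

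The design gives reason to doubt both equalities. Correlation between repeated scores tends to fall as the interval lengthens, and baseline to 6 months is twice as long as either other gap. The delayed arm gains access between the second and third visits. Baseline is taken at entry to a study for which "The aim of this study is to recruit people experiencing symptoms of depression", so its spread need not match that at follow-up.

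At stake are the confidence intervals and tests at the primary time point, and the within-group changes. One of these, from 3 to 6 months in the delayed arm, describes what happens after that arm gets the intervention. Tukey's adjustment changes the critical value; it does not correct a wrong standard error.

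**Working it through.** The article gives no SD, correlation, effect size or standard error, so there is no figure of its own to reproduce. What follows is illustration.

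**Inputs.** From the article: three visits, 50 per arm, at least 70% follow-up judged acceptable for the mood data. Assumed: the SDs and correlations below, two-sided tests, normal approximation.

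**1. Between-group difference at 3 months, complete data.** The model's common variance is about the mean of the three visit variances. The standard error is SD × √(2/50) = 0.2 × SD. The unadjusted error of a nominal 5% test is 2 × P(Z > 1.96 × ratio), where ratio = common SD / true 3-month SD.

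| SDs (baseline/3/6 months) | Common variance | Common SD | Ratio | SE, model vs true | Unadjusted error |
|---|---|---|---|---|---|
| 5/5/5 | 25 | 5.00 | 1.00 | 1.00 vs 1.00 | 5.0% |
| 5/6/6 | (25+36+36)/3 = 32.33 | 5.69 | 0.948 | 1.137 vs 1.200 | 6.3% |
| 5/6.5/6.5 | (25+42.25+42.25)/3 = 36.50 | 6.04 | 0.929 | 1.208 vs 1.300 | 6.9% |
| 6/5/5 | (36+25+25)/3 = 28.67 | 5.35 | 1.071 | 1.071 vs 1.000 | 3.6% |
| 5/5.5/7 | (25+30.25+49)/3 = 34.75 | 5.90 | 1.072 | 1.179 vs 1.100 | 3.6% |

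In the last row both follow-up SDs exceed the baseline SD, yet the 3-month standard error is too large. What matters is the 3-month variance against the three-visit average.

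**2. At 70% follow-up** baseline carries more weight. For 5/6/6 the variance is (25 + 0.7×36 + 0.7×36)/2.4 = 31.42, the SD 5.605 and the ratio 0.934.

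**3. Simulation** (REML random-intercept fits, 1,500 replicates, 100% or 70% follow-up, two correlation patterns). For 5/6.5/6.5, model-to-empirical SE ratios were 0.92–0.94 and unadjusted error 6.5–7.8%. For 6/5/5 the ratios were 1.06–1.12 and the error 2.6–4.3%.

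**4. Within-group changes, equal SDs.** Assume correlations 0.5 (baseline–3), 0.4 (baseline–6) and 0.7 (3–6). The model uses their mean, 1.6/3 = 0.533. The variance of a change is proportional to 2(1 − ρ), and the model gives 2(1 − 0.533) = 0.933 for every pair.

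- Baseline to 3 months: true 1.0; √(0.933/1.0) = 0.966, SE 3% too small, unadjusted error 5.8%.
- Baseline to 6 months: true 1.2; √(0.933/1.2) = 0.882, SE 12% too small, unadjusted error 8.4% (8.7% in 20,000 simulations).
- 3 to 6 months: true 0.6; √(0.933/0.6) = 1.247, SE 25% too large, unadjusted error 1.5%.

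Equal SDs therefore protect the between-group comparisons at a visit, but not the within-group changes.

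**5. Future sample size, only if a pooled SD were used.** With an assumed difference of 3, 90% power and two-sided 5%, n per arm = 2 × (1.960 + 1.282)² × variance / 9. A true 3-month variance of 36 needs 85; the pooled 32.33 gives 76, about 11% too few.

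**The case against.** **Covariance structure is a detail that an article may leave to a fuller plan, and the wording does not exclude visit-specific residual variances.** This stands in part. But the article does state the fixed effects, covariates, multiplicity method and random term, and as stated the model is compound symmetry. A different structure would change what is published.

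**A reader might infer that follow-up scores will spread more, so the 3-month interval is too narrow.** The article does not support this. It gives no SDs, and the eligibility criteria contain no mood-score cut-off that would squeeze baseline. The bias can go either way, and wider 6-month scores alone would raise the pooled variance and push the 3-month standard error upwards.

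**A reader might infer that the future sample size inherits a pooled SD.** The article says only that the 3- and 6-month data will be used. An observed 3-month SD carries none of this bias.

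**A reader might set the 6.3% against the stated 5%.** They are different quantities: 6.3% is an unadjusted per-comparison error, while the article's 5% is familywise after Tukey. If the family were all six group-by-time means (an assumption), the critical value would be about 2.85, and the 3-month per-comparison error under 5/6/6 about 0.7% against 0.4% nominal. No familywise rate was calculated.

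**The consequence is small.** This largely stands. No feasibility criterion rests on an efficacy p-value, and the between-group difference in change from baseline is barely affected in the simulated cases where follow-up spreads more (SE ratio 0.98–1.05). None of this makes the other standard errors right.

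**Conclusion.** The point holds as a minor one. Read as written, the model imposes one variance and one correlation on three visits, and is then used for contrasts whose standard errors depend on visit-specific values. Under the assumed values, 3-month between-group standard errors run from about 7% too small (5/6.5/6.5) to about 7% too large (5/5.5/7) with complete data. Within-group change standard errors run from about 12% too small to about 25% too large, even with equal SDs. If the true variances and correlations were all equal, there would be no error. Neither the direction nor the size can be established from the article. Severity is minor because the primary question is feasibility and no pooled SD is committed to the future sample size.

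**What to change.** Replace the participant random intercept with an unstructured 3x3 within-participant covariance, fitted by REML with Kenward-Roger degrees of freedom. Name heterogeneous compound symmetry as the fallback if it does not converge. State that the future power calculation takes the 3-month SD and the baseline-to-3-month correlation from that matrix or from the observed data, not from a variance pooled over visits.

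The cost is a change of model code and wording, with no new data. The covariance goes from two parameters to six, four more, which is manageable with 100 participants.
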